## Abstract

**Background:**

Uterine fibroids are non-cancerous overgrowths of the smooth muscle in the uterus. As they grow, some cause problems such as heavy menstrual bleeding, pelvic pain, discomfort during sexual intercourse, and rarely pregnancy complications or difficulty becoming pregnant. Multiple treatment options are available. The lack of comparative evidence demonstrating superiority of any one treatment means that choosing the best option is sensitive to individual preferences. Women with fibroids wish to consider treatment trade-offs. Tools known as patient decision aids (PDAs) are effective in increasing patient engagement in the decision-making process. However, the implementation of PDAs in routine care remains challenging. Our aim is to use a multi-component implementation strategy to implement the uterine fibroids Option Grid™ PDAs at five organizational settings in the USA.

**Methods:**

We will conduct a randomized stepped-wedge implementation study where five sites will be randomized to implement the uterine fibroid Option Grid PDA in practice at different time points. Implementation will be guided by the Consolidated Framework for Implementation Research (CFIR) and Normalization Process Theory (NPT). There will be a 6-month pre-implementation phase, a 2-month initiation phase where participating clinicians will receive training and be introduced to the Option Grid PDAs (available in text, picture, or online formats), and a 6-month active implementation phase where clinicians will be expected to use the PDAs with patients who are assigned female sex at birth, are at least 18 years of age, speak fluent English or Spanish, and have new or recurrent symptoms of uterine fibroids. We will exclude postmenopausal patients. Our primary outcome measure is the number of eligible patients who receive the Option Grid PDAs. We will use logistic and linear regression analyses to compare binary and continuous quantitative outcome measures (including survey scores and Option Grid use) between the pre- and active implementation phases while adjusting for patient and clinician characteristics.

**Discussion:**

This study may help identify the factors that impact the implementation and sustained use of a PDA in clinic workflow from various stakeholder perspectives while helping patients with uterine fibroids make treatment decisions that align with their preferences.

**Trial registration:**

Clinicaltrials.gov, NCT03985449. Registered 13 July 2019, https://clinicaltrials.gov/ct2/show/NCT03985449

**Electronic supplementary material:**

The online version of this article (10.1186/s13012-019-0933-z) contains supplementary material, which is available to authorized users.

Contributions to the literature
Our paper will determine the real-world barriers and facilitators to the sustained implementation of patient decision aids.We will provide insight on various processes to identify patients eligible to receive a patient decision aid and *how* and *when* to provide these tools to patients to minimize the burden on clinic workflow.Ultimately, we will delineate pathways that will enable clinics to determine how their workflow needs to change in order to achieve the sustained implementation of a patient decision aid.

## Background

Uterine fibroids, non-cancerous overgrowths of the smooth muscle in the uterus, develop in nearly half of all women of reproductive age [1]. Some uterine fibroids give rise to heavy menstrual bleeding, pelvic pain, discomfort during sexual intercourse, pregnancy complications, and/or difficulty becoming pregnant [1]. Given racial disparities in the US prevalence of symptomatic uterine fibroids, African-American and Latina women may be more likely to experience these issues and also may have poorer treatment outcomes, greater economic burden, and higher incidence of uterine fibroids in comparison to White women [2–5].

Many options are available to treat uterine fibroids including medications, intrauterine devices (with and without hormones), destruction of the inner layer of the uterine wall (endometrial ablation), removal of the uterus (hysterectomy), removal of fibroids (myomectomy), or reducing blood supply to the uterus (uterine artery embolization). However, insufficient evidence exists about the comparative effectiveness of treatments for uterine fibroids [2, 6, 7]. Choosing the best treatment option for uterine fibroids requires women to consider the unique characteristics of each option and weigh which option might best fit her needs and preferences.

Patient decision aids (PDAs) like Option Grid™ can help educate patients to better navigate preference-sensitive treatment decisions [8, 9]. Option Grids (available in text, picture, or online formats) present evidence-based information in a tabular format, so patients can compare options together with clinicians [10]. Across a variety of clinical contexts, Option Grid PDAs increase patient knowledge and shared decision making without significantly increasing encounter duration [11, 12]. A previous version of the uterine fibroid Option Grid increased patient engagement in the clinical conversation, improved knowledge of treatment options, and increased satisfaction with care [13, 14].

Implementation of PDAs remains difficult across a range of healthcare settings [15]. System and organizational barriers relate to incentives, competing priorities, and established behavior patterns [16, 17]. Despite evidence that it is possible to implement PDAs, particularly if implementation is supported by clinical champions, organizational strategies, and effective electronic health record (EHR) integration efforts, more work is needed to determine how best to routinely adopt these tools in clinical practice [18, 19].

We aim to use a multi-component implementation strategy guided by the Consolidated Framework for Implementation Research (CFIR) and the Normalization Process Theory (NPT) to develop a tailored strategy for each of the five participating gynecology settings to implement the uterine fibroid Option Grid PDA. We will (1) assess each site’s organizational readiness for patient engagement, (2) use a tailored implementation strategy to incorporate the uterine fibroid Option Grid in clinical care at each site, (3) examine the characteristics associated with success and failure to implement and sustain Option Grid use in practice, and (4) integrate new evidence into existing clinical practice guidelines where feasible. We will also evaluate the impact of the implementation strategies on clinical and other relevant outcomes for women across socioeconomic strata who seek treatment for symptomatic uterine fibroids. We hypothesize that providing study settings with various formats of PDAs to help tailor the implementation strategy to their clinic workflow will lead to sustained use of PDAs.

## Methods

### Design

We will conduct a randomized stepped-wedge study where randomization of each site to a pre-implementation start date occurs prior to the start of the study (see Fig. 1 for details). The stepped-wedge design with a baseline pre-implementation phase allows for within-site pre/post comparisons. Following the pre-implementation phase, which occurs at a different time point for each site, we will provide a brief initiation session to introduce Option Grid PDAs and how to use them in practice. After initiation, clinicians will be expected to use the intervention in an “active implementation” phase. The SPIRIT checklist (see Additional file 1) guided our protocol development [20].

**Fig. 1 Fig1:**
[figure not shown]
Stepped-wedge study design and timeline

#### Theoretical framework

The multi-component implementation strategy is guided by the CFIR and NPT. CFIR is a pragmatic, multilevel framework that guides the evaluation and design of implementation studies [21, 22]. It comprises five domains (intervention characteristics, outer setting, inner setting, characteristics of individuals, and process) and 39 related constructs. These domains interact with one another to influence the effectiveness of the implementation strategy. In the context of our study, CFIR will be used at a macro level to guide implementation by comprehensively addressing four of the five CFIR domains: intervention characteristics, inner setting, characteristics of individuals, and process. Table 1 provides details on the CFIR domains.

**Table 1 Tab1:** Intervention characteristics that influence implementation success (according to CFIR)

Construct	Short description
I. Intervention characteristics	
A. Intervention source: quality assurance.	EBSCO Systematic Literature Surveillance System (source of evidence for DynaMed Plus product) is best in class.
B. Relative advantage: comparison opportunity	Very few clinicians have used patient decision aids designed to facilitate shared decision making. Our evidence so far indicates that clinical teams are positive about their utility.
C. Adaptability: the degree to which an intervention can be adapted to local needs.	The availability of multiple formats: online and two printed versions (text and Picture Option Grid) allows maximum adaptability to local workflow variations. The online tool can be sent to patients ahead of visits, as well as after visits. The printed versions allow clinicians to tailor the content to local practice variation and to fit the tool into their style of communication with patients of varying literacy and computer literacy levels. We know that clinicians value the ability to add, edit, and make notes on these tools before they give them to patients to take home. The use of pictures maximizes the usability and accessibility of this approach across socioeconomic strata.
D. Trialability: local test	The cost or complexity of using Option Grid is low, and so, we anticipate low resistance to trialability by the participating clinical teams. In other clinical contexts, we have experienced zero resistance to trialability.
E. Complexity: as the number of steps, or the number of people or processes increases, so does the difficulty of implementation.	The Option Grid has been designed to be fast, frugal, and outwardly simple, so that it can fit into decision discussions that will benefit from accurate, accessible information.
F. Design quality and packaging: instills confidence in the intervention.	The EBSCO Option Grid has achieved high quality design with professional user centered graphic design.
G. Cost: investment, supply, and opportunity costs.	Investment will be related to the time taken to learn how to integrate the tool into the clinical workflow, a learning curve that has been observed to take a few interactions. The project will ensure adequate supply; future use will need to ensure online access for sustainability. We anticipate minimal disruption on opportunity costs—clinicians typically cover the type of information in Option Grids. The tool makes the exchange more efficient according to our evaluations. Evidence suggests that Option Grid decision aids do not typically increase consultation time as the content of the tool is information clinicians already provide to patients routinely.
II. Inner setting	
B. Networks and communication: The nature and quality of webs of social networks and the nature and quality of formal and informal communications within an organization.	Eligible patients will be identified using the site’s outpatient scheduling system in advance of their visit. Where possible, the eligible patients will be sent an Option Grid in advance of their appointment and will be instructed to bring the Option Grid to their appointment.
C. Culture: Norms, values, and basic assumptions of a given organization.	We want to help implement a process where patients are engaged in their treatment decisions “upfront” by receiving an intervention that can facilitate a discussion with their clinician regarding their treatment options.
D. Implementation climate: The absorptive capacity for change, shared receptivity of involved individuals to an intervention, and the extent to which use of that intervention will be rewarded, supported, and expected within their organization.	We will assess implementation climate by calculating the expected use of the intervention which is based on the volume of patients visiting each site who have been diagnosed with symptomatic uterine fibroids.
E. Readiness for implementation: Tangible and immediate indicators of organizational commitment to its decision to implement an intervention.	We will determine readiness for implementation from the Measuring Organizational Readiness for patient Engagement (MORE) survey which will be administered prior to the commencement of the pre-implementation phase to 10 stakeholders at various levels of the service delivery team (i.e., clinicians, administrators, managers).
III. Characteristics of individuals	
A. Knowledge and beliefs about the intervention: Individuals’ attitudes toward and value placed on the intervention as well as familiarity with facts, truths, and principles related to the intervention.	ADOPT is a measure of patient attitudes to patient decision aids. Clinicians will be asked to select one or more words that best describes their attitudes to the potential use of patient decision aids from a pool of ten words.
B. Self-efficacy: Individual belief in their own capabilities to execute courses of action to achieve implementation goals.	The words selected by the participating clinicians who complete the ADOPT measure will be indicative of their self-efficacy or the belief in their ability to execute the course of action and achieve implementation goals.
C. Individual stage of change: Characterization of the phase an individual is in, as he or she progresses toward skilled, enthusiastic, and sustained use of the intervention.	We will compare collaboRATE scores (three-item patient-reported outcome measure) before and after the initiation phase to determine individual stage of change.
D. Individual identification with organization: A broad construct related to how individuals perceive the organization, and their relationship and degree of commitment with that organization.	Ten stakeholders at various levels of the service delivery team (i.e., clinicians, administrators, managers) at each site will complete the Measuring Organizational Readiness for patient Engagement (MORE) survey.
E. Other personal attributes: A broad construct to include other personal traits such as tolerance of ambiguity, intellectual ability, motivation, values, competence, capacity, and learning style.	Personal attributes will be determined via the ADOPT survey. Clinicians will circle up to 10 words that will be indicative of their personal traits.
IV. Process	
A. Planning: The degree to which a scheme or method of behavior and tasks for implementing an intervention are developed in advance and the quality of those schemes or methods.	We will be visiting each site multiple times throughout the study to provide support and assess the degree to which each site is willing to adopt our processes.
B. Engaging: Attracting and involving appropriate individuals in the implementation and use of the intervention through a combined strategy of social marketing, education, role modeling, training, and other similar activities.	Our second site visit will aim to attract and involve appropriate individuals in the implementation and use of the intervention. In addition, we will be providing initiation to clinicians to teach them how to use the tools in practice. Each site will also have a “clinical champion”/site principal investigator that will support the implementation of the intervention. The strategy will also include feedback on study processes from the members of the Community Advisory Board.
C. Executing: Carrying out or accomplishing the implementation according to plan.	The primary outcome measure is the number of eligible patients who receive the uterine fibroid Option Grid.
D. Reflecting and evaluating: Quantitative and qualitative feedback about the progress and quality of implementation accompanied with regular personal and team debriefing about progress and experience.	A 23-item instrument—NoMAD Normalization Process Theory (NPT) survey—will be used to capture the perspective of professionals directly involved in the work of implementing the intervention. We will also conduct semi-structured interviews with a convenience sample of clinicians and staff at each of the five clinical sites to identify, monitor, and assess the progression and integration of the intervention and to determine the utility of the Option Grid patient decision aid and the barriers and facilitators to their integration in the clinic workflow. We will also be receiving feedback at our annual site visit to determine the process each site is using to facilitate implementation of the intervention. The outcomes we will be measuring include the extent to which tools are delivered, the extent to which patients are reporting use of Option Grid in appointments, and the collection of collaboRATE scores.

In addition to CFIR’s multilevel approach, NPT will be used at a micro level to focus on the dynamic process that leads to the successful implementation of an innovation in routine clinical practice. NPT is an explanatory theory that helps evaluators understand the process by which organizations embed interventions into their normal work [23, 24]. NPT has four theoretical tenets: (i) coherence, supports individual and collective consensus about an intervention and its purpose; (ii) collective action, the tasks allocated to the various members within the organization to build and sustain use; (iii) cognitive participation, the relational work that influences “implementation and legitimation”; and (iv) reflexive monitoring, the communal appraisal work that aids assessment of the intervention [25].

### Setting

The five study sites are gynecology clinics at (i) Dartmouth-Hitchcock Medical Center in Lebanon, New Hampshire; (ii) Barnes-Jewish Hospital in St. Louis, Missouri; (iii) Montefiore Medical Center in Bronx, New York; (iv) Brigham and Women’s Hospital in Boston, Massachusetts; and (v) Mayo Clinic in Rochester, Minnesota.

### Participants

We will include physicians (attending or resident) who consent to participate in our implementation study and provide care to women with symptomatic uterine fibroids during the project duration at participating sites.

We will include patients showing new or recurrent symptoms of uterine fibroids (e.g., heavy menstrual bleeding, pelvic pressure or pain) who are seeking treatment and meet all of the following inclusion criteria: (i) assigned female sex at birth, (ii) at least 18 years of age, (iii) speak English or Spanish, and (iv) have the ability to complete short surveys online independent of assistance. We will not exclude pregnant patients. We will exclude postmenopausal patients because they may have different treatment options than those presented in the Option Grid PDA used in this study.

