### Intervention

To facilitate deliberation about treatment options, the uterine fibroid Option Grid PDA is organized in a tabular format and is based on patients’ frequently asked questions, which were sourced by analyzing the research literature and by qualitative inquiry with stakeholders including gynecologists and 10 women experiencing symptoms of uterine fibroids.

The uterine fibroid tool is one of over 22 Option Grid decision aids developed and maintained by EBSCO Health. We helped EBSCO adapt the Option Grid for this study by following a multi-step Community Based Participatory Research (CBPR) approach. The tool (as of May 2019) compares seven treatment options (watch and wait, medicine with hormones, medicine without hormones, uterine artery embolization, endometrial ablation, myomectomy, and hysterectomy) and consists of answers to six frequently asked questions: (1) What does it involve? (2) Will I have less bleeding and pain? (3) Will the fibroids go away or get smaller (in size)? (4) Is it safe to get pregnant? (5) What are the side effects? and (6) What are the more serious risks? The uterine fibroid Option Grid is designed to be accessible to patients across socioeconomic and health literacy strata using plain language (readability of 6th grade or less). See Fig. 2 to view the text version of the Option Grid.

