### Outcomes and data collection

#### Primary outcome measure

The primary outcome measure is the number of eligible patients who receive the uterine fibroid Option Grid (three formats available).

Eligible patients will be identified in advance by the project team at each site through their outpatient scheduling systems. This process will enable us to determine the total number of patients who are eligible to participate in the study (the denominator). To calculate the number of patients who receive an Option Grid (numerator), we will provide each site with a box filled with text and Picture Option Grid paper pads. Pads will be available in every consultation room within each sites’ obstetrics-gynecology clinic. To use a paper-based Option Grid, the clinician will tear it from the pad and a numbered stub will remain where they will write their name and indicate if they are an attending clinician or a resident (see Fig. 3 for a mockup of the paper pad stub). The research assistant at each site will refer to the numbered stubs to document the number of patients who received an Option Grid on a weekly basis. The research assistant will keep a log of the numerator and denominator in an Excel file and will report the data back to the Dartmouth project staff on a weekly basis via the Qualtrics database.

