
**Table 2 Tab2:** Implementation sustainability outcome measures for patient outcomes

	Implementation phases		
	Pre	Active	Sustainability
Organizational readiness (Measuring Organizational Readiness for patient Engagement survey)	✓		
Clinician attitudes to PDAs (ADOPT: Attitudes toward Decision Aids fOr PatienTs survey)	✓	✓	✓
Percentage of eligible patients receiving intervention (primary outcome measure)	✓	✓	✓
Quality of shared decision-making process using Observer OPTION-5	✓	✓	
Utility of tools and approach (clinician interviews)		✓	✓
Normalization Process Theory: NOMAD Toolkit (interviews)	✓		✓
Intervention fidelity assessment using observer checklist		✓	
Patient outcomes			
Uterine Fibroid Symptom and Health-Related Quality of Life Questionnaire (UFS-QOL) symptom severity subscale (8-items)	✓	✓	
**collabo**RATE (three items)	✓	✓	
The Comprehensive Score for financial Toxicity (COST)—one selected item	✓	✓	
Resource utilization (ambulatory and hospital visits)	✓	✓	
Intended and received treatment	✓	✓	
Chew health literacy measure (one item)	✓	✓	
Patient demographics (email address, health insurance status, age, race, gender, and spoken language)	✓	✓	

Throughout the pre- and active implementation phases, eligible patients at each site will be invited by clinic staff to take a survey on a tablet computer following their clinical encounter (see Additional file 2 to view the patient survey). Clinic staff may provide the patient with the tablet computer or refer them to a kiosk located in the clinic that will contain the tablet. At the start of the survey, patients will be given the opportunity to view the study information and provide consent to participate in the study. The survey will collect the following patient-reported outcomes, in addition to the patient’s email address which will be used to send patients a WebLink to the follow-up survey 3 months after their first survey is completed. The follow-up survey can be completed on a personal computer or mobile device. We anticipate that approximately 30% of eligible patients will complete the post-encounter survey. The following is a list of patient-reported outcomes that we will be assessing:

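### As written, a survey-ability criterion is part of the eligibility that forms the primary reach denominator, although counting receipt of the Option Grid needs no patient survey

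*Protocol article*

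**What the plan says.** The Participants section lists four criteria for patients with new or recurrent symptoms who are seeking treatment, and they must "meet all of the following inclusion criteria". The fourth, criterion (iv), is that they "have the ability to complete short surveys online independent of assistance". Postmenopausal patients are excluded.

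The Primary outcome measure section states: "The primary outcome measure is the number of eligible patients who receive the uterine fibroid Option Grid (three formats available)". It names the denominator as "the total number of patients who are eligible to participate in the study (the denominator)" and gives its source: "Eligible patients will be identified in advance by the project team at each site through their outpatient scheduling systems". Table 2 expresses the same outcome as a percentage: "Percentage of eligible patients receiving intervention (primary outcome measure)".

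The numerator comes from numbered pad stubs, on which the clinician writes a name and whether they are an attending or a resident. Where the online tool is available through the health record, weblog data are added.

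On the intended users, the Intervention section describes the tool as "designed to be accessible to patients across socioeconomic and health literacy strata". Table 1, under Adaptability, says the printed versions help clinicians fit the tool into their "communication with patients of varying literacy and computer literacy levels".

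**The concern.** The primary outcome is a measure of reach: of the patients who should get the tool, how many do. Its denominator should therefore be the patients to whom the tool is to be offered. The article uses one definition of eligibility both for this purpose and for the patient survey, and that definition contains a condition that matters only for the survey.

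Two things are at stake. First, the reported proportion may not describe the population for whom several formats, including paper, are provided. Second, numerator and denominator may be counted over different groups, in which case the proportion is not a valid estimate of reach in either.

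**Working it through.** The article states no figure for this point, so there is none to reproduce. The check sets the definitions side by side and then works out the arithmetic of a mismatch.

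**1. The chain of definitions.** Criterion (iv) is required for eligibility (Participants). Eligibility to take part is the denominator (Primary outcome measure). No section gives a separate definition for reach. The Secondary outcome measures section uses the same term as the base for its expected 30% survey completion. So, as written, (iv) restricts the reach denominator.

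**2. What the outcome needs.** Receipt is counted from stubs and weblogs; the patient supplies nothing. Table 2 also ticks the primary outcome in the sustainability phase, where it ticks no patient-survey outcome. In that phase (iv) supports no data collection, yet still decides who is counted.

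**3. Who is offered the tool.** The Abstract's list of patients with whom clinicians should use the tool omits (iv). Table 1, under Implementation climate, bases expected use on the volume of patients diagnosed with symptomatic fibroids. Both populations are wider than the one in Participants.

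**4. Whether (iv) can be applied.** Eligibility is established before the visit from scheduling systems. The article describes no way of reading unaided survey ability there. That such systems do not hold it is an inference, though a reasonable one.

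**5. Arithmetic.** Let u be the share of otherwise eligible patients who cannot complete an online survey unaided, rA the reach in those able, and rU the reach in those unable. None of these is in the documents; all values below are assumptions.

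- True reach in everyone: R = (1 − u) × rA + u × rU.
- *Denominator restricted, stubs counting everyone:* the reported value is R / (1 − u). The inflation factor 1 / (1 − u) does not depend on rA or rU. With R = 0.50:
  - u = 5%: 0.50 / 0.95 = 0.526
  - u = 10%: 0.50 / 0.90 = 0.556
  - u = 20%: 0.50 / 0.80 = 0.625
  - u = 25%: 0.50 / 0.75 = 0.667
- *Both restricted:* the reported value is rA, and it differs from R by u × (rA − rU). With u = 20% and rA = 0.50:
  - rU = 0.25: 0.20 × 0.25 = 0.05 too high
  - rU = 0.50: no difference
  - rU = 0.60: 0.20 × (−0.10) = −0.02, that is, too low
- *Criterion not applied anywhere:* the reported value is R, with no distortion, but the denominator then does not match the stated eligibility.

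**6. Whether the pre/active comparison removes the problem.** The Pre-implementation phase section says the Option Grid is not used in that phase. Receipt before implementation is then zero by design, so the contrast between phases equals the active-phase proportion, and an error in that proportion passes straight into it.

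**The case against.** The strongest reply is that the restriction may never operate. If a scheduling system cannot show survey ability, the team building the denominator cannot remove anyone for lacking it, and the patients concerned are probably counted. The article is also condensed, and screening steps belong in the full protocol. This stands as far as it goes: nothing shows that patients will in fact be removed. It does not settle the matter, because the article itself fixes both the eligibility list and the denominator, and following them gives a narrower population than intended.

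The Abstract's omission of (iv) is weak evidence on its own, since that list also leaves out treatment-seeking. Table 1 and the stub count carry more weight.

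Differences between sites in how (iv) is handled matter less for within-site comparisons and models with site-fixed effects. That holds for survey outcomes measured in both phases, but less so for an outcome that is zero at baseline.

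A reader might infer three stronger things that the documents do not support:

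- *That the tool targets low-literacy patients and the plan removes them.* The text says it is accessible across strata. Unaided online survey ability is only a proxy for literacy, and the Chew items ask about needing help with reading, so some respondents with lower literacy are still expected.
- *That analyses by health literacy would be repaired by changing the denominator.* Literacy is collected only in the patient survey, to which (iv) would still apply.
- *That reach is overstated by a known number of points.* The share unable and their reach are not given, and the difference may be zero or reversed.

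**Conclusion.** The point holds as a fault of definition in the primary outcome. A survey-participation criterion is, by the article's wording, part of the reach denominator; it has no function for that outcome and sits badly with the stated audience. In operation the denominator may be restricted, unrestricted or handled differently by site, and it is paired with a stub count for which the text describes no patient eligibility check.

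The size depends on which of these happens. If only the denominator is restricted, reach is inflated by a factor of 1 / (1 − u), for example from 0.50 to between 0.526 and 0.667 for assumed shares of 5% to 25%. If both parts are restricted, the estimate omits this group, and neither direction nor size can be derived from the documents. If the criterion is ignored, there is no bias, only a mismatch between the protocol and what is reported. The step from scheduling systems to inconsistent application is an inference.

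**What to change.** Define the reach denominator by symptoms, treatment-seeking, sex, age, language and non-postmenopausal status only. Count the numerator over that same population, and state how stubs and weblog records will be limited to it. Apply criterion (iv) only to the patient-survey outcomes. Align the Abstract, the Participants section and the Primary outcome measure section so that the same population appears in each.

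The change to the denominator is a minor wording amendment and needs no new patient data. Tying the stub count to eligible patients may need a small addition to the weekly log that the research assistants already keep. The downside is that reported reach may be slightly lower.
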